### Data collection and management

Outcome assessment at baseline and at the end of the visit will be conducted by a research nurse blinded to the patient allocation in order to reduce potential detection bias. A chart review will take place by the research nurse to ascertain demographic details. Outcome assessment at follow-up (30 days, 4 months and 6 months following the index visit) will be conducted via a telephone call.

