### Setting

The study will take place in the ED of the UHL, a regional hospital with a large catchment area in the western region of the Republic of Ireland. Follow-up assessment will take place via telephone interviews.

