### Power calculation

We estimated our sample size based on our primary outcome (ED length of stay) using G*Power version 3.1. Using data from the Patient Experience Time (PET) database employed in the ED at UHL, the average ED length of stay for patients aged 65 and older for the period 2016–2017 was 13.95 h (standard deviation 12.49 h) [14]. Estimating a 40% decrease in ED length of stay in the intervention group (mean 8.37 h), and with a 20% attrition rate to follow-up, a sample size of 258 patients (129 in each group) is required to achieve 90% power with two-tailed tests at an alpha level of 0.05.

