### Outcomes

A range of outcomes will be assessed to identify the potential impact of the intervention on quality, safety, and clinical- and cost-effectiveness of care. The primary outcome of the study is duration of patient ED stay (mean number of hours from time of arrival to discharge or admission). The secondary outcomes include the rates of hospital admissions from the ED (defined as the proportion of patients who are admitted to hospital after their index visits), the duration of hospital admission after the ED index visit, as well as the number of ED re-attendances, nursing home admissions, unplanned hospital visits (and duration of stay) and mortality within 30 days, 4 months and 6 months of the initial index visit. Healthcare utilisation (visits to a general practitioner (GP), public health nurse, home help, private consultation, outpatient department visit, or allied health services) will also be captured at 30 days, 4 months and 6 months after the index visit. Assessment of patient-oriented outcomes include the Barthel Index for Activities of Daily Living [15] as a global measure of function and the EuroQoL’s 5-level of the EQ-5D (EQ-5D-5 L) to measure health-related quality of life [16], which will be conducted at baseline as well as at follow-up (30 days and 6 months, with quality of life also assessed at 4 months).

In addition, patient satisfaction with their index visit will be explored using the 18-item Patient Satisfaction Questionnaire (PSQ-18) [17] at the time of the visit.

An economic analysis will estimate the incremental cost-effectiveness of the HSCP team from the perspective of the Irish public health service, compared with usual care. We will estimate healthcare costs from reference costs from national data sources. Participants’ responses to the EQ-5D-5 L questionnaire will be used to estimate health state utilities using the Irish value set [18], and quality-adjusted life years (QALYs) for each treatment group will be estimated across all time points.

Finally, a process evaluation will be conducted through a mixed quantitative–qualitative design to describe the implementation of the intervention as well as investigate the mechanisms and contextual influences of the implementation as perceived by the HSCP team and representation from the wider ED staff. A detailed study protocol for the process evaluation is available elsewhere [19].

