## Discussion

Based on the results of a systematic review [6], this is the first randomised controlled trial to examine the impact of an HSCP team on the quality, timeliness and cost-effectiveness of care of older adults in the ED when compared with usual care. Previous randomised controlled studies have focused mainly on single HSCPs working as members of ED teams [21, 22], while studies that have described HSCP teams have employed nonrandomised designs [23, 24]. Our study employs a controlled and robust design which is the most appropriate to demonstrate the efficacy of this model of care. The range of outcomes assessed in the study will enable us to provide detailed conclusions on the impact both at the patient and process levels. Furthermore, we will provide information on effectiveness both through a cost analysis and a qualitative investigation of feasibility involving ED staff members. The findings of the study will offer useful recommendations for future implementation.

A potential issue related to the study includes the fact that, due to the nature of the intervention, patients and ED staff members involved in the study cannot be blinded to allocation. While this may increase the risk of performance bias, an open procedure reflects realities of clinical practice in the ED. Another issue is linked to the working hours of HSCPs (8 am to 5 pm Monday to Friday) which may result in missing eligible patients who present out of these hours. However, we will capture crude estimates of these presentations to report the generalisability of the trial. Furthermore, as agreed with the team and the ED medical/nursing staff before the commencement of participant recruitment, the HSCP team’s scope will be limited only to patients involved in the trial; however, a risk of contamination cannot entirely be ruled out as ED medical and nursing staff collaborating with the HSCP team could be influenced in their procedures if taking care of patients in the control group.

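### The plan names only telephone contact with unblinded patients as the source for follow-up re-attendances, hospital visits and deaths; the study hospital's own records should be added.

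*Protocol article*

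**What the plan says.** The route for follow-up is given twice in the protocol article. Setting has "Follow-up assessment will take place via telephone interviews", and Data collection and management has "Outcome assessment at follow-up (30 days, 4 months and 6 months following the index visit) will be conducted via a telephone call".

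The outcomes due at those calls, listed under Outcomes, include the "number of ED re-attendances, nursing home admissions, unplanned hospital visits (and duration of stay) and mortality within 30 days, 4 months and 6 months". Community healthcare utilisation, the Barthel Index and the EQ-5D-5L are also collected during follow-up.

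Two hospital sources are mentioned, each for another purpose:
- Charts: "A chart review will take place by the research nurse to ascertain demographic details".
- The ED database, in Power calculation, as the source of the planning mean and SD: "Using data from the Patient Experience Time (PET) database employed in the ED at UHL".

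On blinding, the Discussion says that "patients and ED staff members involved in the study cannot be blinded to allocation". Data collection and management describes a blinded assessor for two time points: "Outcome assessment at baseline and at the end of the visit will be conducted by a research nurse blinded to the patient allocation". It says nothing about who makes the follow-up calls or whether that person is blinded.

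**The concern.** Re-attendance, admission, days in hospital and death are events that a hospital can usually establish without asking the patient. As written, they depend on what unblinded older people can report, and eligibility extends down to an MMSE of 17 (Participants). Two weaknesses follow.

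- **Misreporting.** Visits and lengths of stay may be forgotten or misdated. If knowing the allocation changes what is reported, the error differs between arms.
- **Missingness linked to the event.** Patients cannot report their own death, and an inpatient may not answer the telephone. An unanswered call may therefore itself reflect the outcome.

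The Data analysis section estimates ED re-visits, unplanned admissions, nursing home admissions and healthcare utilisation as odds ratios, adjusted at follow-up for age and ISAR. That adjustment handles baseline differences in risk. It does not repair an outcome that is wrongly reported, or missing because the event occurred. The same utilisation data would presumably feed the costs and the ICER. Mortality is not in the list of logistic-regression outcomes, but it is a stated outcome and is the one least suited to self-report.

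**Working it through.** **1. Recall window.** Calls are at 30 days, 4 months and 6 months. The intervals are about 1 month (index visit to first call), 3 months (first to second) and 2 months (second to third). The longest scheduled recall is therefore about 3 months. It lengthens only if a call is missed.

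**2. Where the 20% comes from.** Power calculation gives a mean of 13.95 h, SD 12.49 h, intervention mean 8.37 h, 90% power and two-sided alpha 0.05.
- Difference = 13.95 − 8.37 = 5.58 h; d = 5.58 / 12.49 = 0.447.
- Two-sample t test: 106.26, so 107 per arm.
- With the allowance: 107 × 1.2 = 128.4, so 129 per arm and 258 in total, which matches the plan.

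The 20% is thus an allowance inside the ED length-of-stay calculation. It is not a forecast for each follow-up event. Steps 3 and 4 apply it to follow-up as an assumption.

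**3. Loss and precision if 20% applied.**
- 0.20 × 258 = 51.6, about 52 patients. For the Abstract's target, 0.20 × 320 = 64.
- Interval width relative to complete data: 1 / √0.8 = 1.118, about 12% wider.

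**4. Power for a follow-up event.** The article gives no event rates, so a range of control risks is assumed, each halved in the intervention arm, with N = 320.

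| Assumed control risk | Power, no loss | Power, 20% loss |
|---|---|---|
| 10% | 40% | 33% |
| 20% | 71% | 61% |
| 30% | 90% | 82% |
| 40% | 98% | 94% |

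**5. Illustrations of bias. All rates are assumed.**
- *Event-related loss, equal in both arms.* With 30% risk among those reached, 20% loss, and 30%, 40% or 50% risk among those missed, the true rate is 0.8 × 30% + 0.2 × (30%, 40% or 50%) = 30%, 32% or 34%. The calls show 30% throughout.
- *Event-related loss, unequal.* With 30% risk among those reached and 50% among those missed, 15% loss gives 0.85 × 30% + 0.15 × 50% = 33%, and 25% loss gives 0.75 × 30% + 0.25 × 50% = 35%. Both arms show 30%, so a real 2-point difference is masked. The true odds ratio is (0.33/0.67) / (0.35/0.65) = 0.91, read as 1.0.
- *Misreporting.* With a true risk of 30% in both arms and 90% versus 80% of events reported, the reported rates are 27% and 24%. The odds ratio is (0.27/0.73) / (0.24/0.76) = 1.17, or 0.85 with the arms reversed, with no true effect. Equal reporting of 90% in both arms gives 1.00.

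For scale, with 160 per arm and a risk near 34%, the 95% half-width for a risk difference is 1.96 × √(2 × 0.34 × 0.66 / 160) = 0.104, about 10 points.

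**The case against.** The strongest reply is that this is a condensed article. Data collection and management is three sentences long and names no source even for ED length of stay, which can hardly come from a follow-up call. Its silence on records therefore does not prove that they will go unused, and the sentence on chart review does not say that demographics are its sole purpose. This stands as far as it goes. However, the follow-up route is not left open: it is stated twice, as telephone, with no other source beside it.

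A reader might also infer more than the article supports:
- *That the ED database and charts hold these events for nearly everyone randomised.* The article shows only that the database yields ED stay times for patients aged 65 and over and that charts are available. Events at other hospitals, and deaths at home or in a nursing home, need not be in either.
- *That patients must recall 6 months.* The call schedule limits this to about 3 months when calls are completed.
- *That one fifth of event data will be lost, mostly in patients with events.* The 20% is a planning allowance, and concentration of loss is plausible but not documented.
- *That unequal loss creates a spurious effect.* In the example above it hides a true difference, and 2 points is small beside a half-width of about 10.

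Finally, the primary outcome is complete at the end of the index visit, and calls are needed anyway for function, quality of life and community use. Both points are right, and they limit the weight of the concern.

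**Conclusion.** The concern holds as a weakness in how secondary outcomes are ascertained. The stated route for re-attendances, unplanned hospital visits with duration, and deaths is self-report by unblinded patients. Some of the patients with these events may be unable to report them, and the planned covariate adjustment does not address that.

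The size that can be stated is conditional. If the 20% allowance carried over to follow-up, about 52 of 258 or 64 of 320 patients would lack these data and intervals would be about 12% wider. The direction and size of any bias cannot be derived from the article; the figures in step 5 of the working show only how it could arise. ED length of stay is untouched. The change is worth making but does not put the main comparison at risk.

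**What to change.** For all randomised patients, and where consent and data-protection approval allow, take ED re-attendance, unplanned admission, days in hospital and in-hospital death at the study hospital from its ED database and charts. The extraction should be done without knowledge of allocation where possible.

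Keep the telephone call for events at other hospitals, community utilisation, Barthel and EQ-5D-5L. Establish deaths elsewhere through a proxy or by confirmation with the GP, who under Monitoring is already told of participation. State whether the callers are blinded to allocation.

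The cost is some extra look-up time for the research nurse, who already reviews charts, and a check that the consent obtained covers record extraction. That check matters because Trial status reports recruitment closed on 31 May 2019. The look-up itself can be retrospective, and follow-up was expected to run to November 2019. Records will still miss events elsewhere, so the report should give the source of each event and the number of patients with records only, a call only, both or neither.

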### Data analysis

Each participant in the study will be assigned a numerical code in order to link data collected at baseline to the data collected at the follow-up at 30 days, 4 and 6 months. Aggregate data will be anonymised. Appropriate descriptive statistics will be used to describe the baseline characteristics of study participants. These will include proportions, percentages, ranges, means and standard deviations, and medians and interquartile ranges (where data are not normally distributed). Differences between the two groups in terms of ED length of stay and hospital length of stay will be analysed using an independent samples *t* test if they meet the assumptions of normality; otherwise, we will employ the nonparametric alternative Wilcoxon Mann–Whitney test with bootstrapping to calculate an effect size 95% confidence interval (CI). The risk of hospital admission rates after the index visit, as well as ED re-visits, unplanned hospital admissions, nursing home admissions and healthcare utilisation at follow-up, will be estimated as odds ratios with 95% CI using a logistic regression, with analyses on follow-up measures adjusted for patient’s age and Identification of Seniors at Risk (ISAR) score at baseline. Patient functioning and quality of life at follow-up will be explored through an analysis of covariance (ANCOVA) adjusting for patient age, baseline ISAR score, baseline Barthel index (for function) and baseline quality of life (for quality of life). Differences in patient satisfaction with their index visit will be analysed using an independent samples *t* test with 95% CI.

For the cost-effectiveness analysis, and as per the Irish Health Information and Quality Authority (HIQA) guidance [20], the primary endpoint of the cost-effectiveness analysis will be costs, QALYs and the incremental cost-effectiveness ratio (ICER). Analysis of uncertainty of the joint distribution of cost and QALYs between the two arms of the study will be presented on a cost-effectiveness acceptability curve to indicate the probability that the HSCP intervention will be cost-effective, based on available trial data and across various willingness-to-pay thresholds.

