### Participants

All adults aged ≥65 years who present to the ED at the UHL between December 2018 and May 2019 (inclusive) are considered eligible for inclusion to the study provided that they meet the following inclusion criteria: 1) the capacity (Mini-Mental State Examination ≥17) and willingness to provide informed consent; 2) baseline mobility and functional status; and 3) are medically stable (where relevant, see Table 1) and presenting with any of the complaints presented in Table 1 as per the Manchester Triage System 2–5 [13].

**Table 1 Tab1:** Presenting complaint as per Manchester Triage System [13]

Before medical work-up*	After medical work-up**
Limb problems	Chest pain
Falls	Shortness of breath
Unwell adult	Abdominal pain
Back pain	Headache
Urinary problems	
Ear and facial problems	

*The health and social care professional (HSCP) team will proactively treat these individuals without prior assessment by a physician

**The HSCP team will await medical clearance prior to assessment and intervention

The exclusion criteria are: 1) aged under 65 years; 2) medically unstable; 3) neither the patient nor the carer can communicate in English sufficiently to complete consent or baseline assessment; and 4) presentation and discharge outside of HSCP operational hours (similar to other studies, the HSCP team is operational between the hours of 8 am and 5 pm Monday to Friday and, therefore, individuals who present to the ED and are discharged outside of these hours will not be included in the study).

This study is pragmatic in nature and, to reflect the realities of clinical practice in the ED, both the triage nurses and treating physicians will act as gatekeepers at the UHL site and inform eligible participants about the study. This method was chosen as the medical condition of participants will change over the course of the index admission.

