### Randomisation

Should participants explicitly consent to participate in the study, they will undergo a baseline assessment of function and quality of life by the research nurse or a member of the HSCP team. To minimise the possibility of selection bias, a researcher independent of the recruitment process (MC) will complete random group allocation. Computer-generated random numbers in blocks of 20 will be created using an internet-based system (https://www.randomizer.org/); the allocation equivalent to each number will be written in a sheet that will be placed in sealed opaque envelopes. These numbers will be stored in the pre-sealed envelopes in a locked drawer in the ED. Allocation will be revealed by the research nurse employed in the trial after recruitment of eligible participants and after conducting the baseline assessment. Allocation will be revealed by accessing and opening the next envelope in the sequence and providing the randomisation information simultaneously to the research team and patient. After allocation is revealed, participants will either receive the HSCP intervention or routine care (the control group).

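### The primary comparison of ED length of stay uses no covariates, although age and baseline ISAR adjust the modelled follow-up outcomes: valid, but a cheap efficiency gain goes unused

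*Protocol article*

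**What the plan says.** The Outcomes section defines the primary endpoint on the scale of mean hours: "The primary outcome of the study is duration of patient ED stay (mean number of hours from time of arrival to discharge or admission".

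The Data analysis section gives it a two-sample test: "Differences between the two groups in terms of ED length of stay and hospital length of stay will be analysed using an independent samples" (a t test, when normality holds). The fallback reads "otherwise, we will employ the nonparametric alternative Wilcoxon Mann–Whitney test with bootstrapping to calculate an effect size 95% confidence interval (CI". Neither test takes covariates, and no adjusted analysis of ED stay is mentioned.

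The binary outcomes have a logistic regression, "with analyses on follow-up measures adjusted for patient’s age and Identification of Seniors at Risk (ISAR) score at baseline". Admission after the index visit stands in the same sentence but is not a follow-up measure, so on a plain reading it is unadjusted. Function and quality of life at follow-up have this model: "analysis of covariance (ANCOVA) adjusting for patient age, baseline ISAR score, baseline Barthel index (for function) and baseline quality of life (for quality of life".

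The Randomisation section says "Computer-generated random numbers in blocks of 20 will be created using an internet-based system" and names no stratification factor. Allocation is revealed only after the baseline assessment.

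The Participants section admits Manchester triage categories 2 to 5 and divides presenting complaints into two pathways in Table 1. For one, the footnote reads "The health and social care professional (HSCP) team will proactively treat these individuals without prior assessment by a physician"; for the other, the team waits for medical clearance.

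**The concern.** The plan treats age and ISAR as worth adjusting for in its modelled secondary follow-up outcomes, yet leaves the outcome that decides the trial as a crude comparison, and it gives no reason for the difference. With no stratification in the design, nothing beyond simple blocking balances prognostic factors between the arms. Any variance in ED stay that baseline data could explain stays in the standard error.

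What is at stake is the width of the primary confidence interval and, above all, power if the true effect is smaller than the 40% reduction assumed. The validity of the primary test is not at stake.

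**Working it through.** **Inputs.** From Power calculation: mean 13.95 h, SD 12.49 h, 40% reduction (to 8.37 h), 20% attrition, 90% power, two-sided alpha 0.05, 129 per group. From the Abstract: recruitment target 320, taken here as 160 per arm. Assumed, because the protocol gives no figure: R² of the baseline covariates on ED hours, range 0.02 to 0.20. A common SD in both arms is also assumed.

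**1. The plan's own figure.** Difference = 13.95 − 8.37 = 5.58 h; d = 5.58/12.49 = 0.447. A two-sample t test (noncentral t) needs 107 per arm for 90% power. 107 × 1.2 = 128.4, rounded up to 129 per arm, 258 in total. The sample size and the unadjusted test therefore agree with each other.

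**2. Which n applies.** The 20% attrition is described as loss to follow-up. ED stay ends at discharge or admission on the index visit, so telephone follow-up losses do not remove it. The relevant sizes are 129 and 160 per arm, not 129 × 0.8 ≈ 103.

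**3. Effect of adjustment.** SE = 12.49 × √(1 − R²) × √(2/n). Power ≈ Φ(difference/SE − 1.96). For example, at n = 160 and R² = 0, SE = 12.49 × √(2/160) = 1.396 h; at R² = 0.10 it is 1.325 h. A 30% reduction is 0.30 × 13.95 = 4.185 h.

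| R² | SE ratio | n per arm for 90% power | Power, 129/arm, 5.58 h | Power, 160/arm, 5.58 h | Power, 160/arm, 4.185 h |
|---|---|---|---|---|---|
| 0 | 1.000 | 106 | 94.8% | 97.9% | 85.0% |
| 0.02 | 0.990 | 104 | 95.2% | 98.1% | 85.7% |
| 0.05 | 0.975 | 101 | 95.7% | 98.4% | 86.8% |
| 0.10 | 0.949 | 95 | 96.6% | 98.8% | 88.5% |
| 0.20 | 0.894 | 85 | 98.0% | 99.4% | 91.8% |

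These use the normal approximation. The noncentral t gives nearly the same: 94.7% and 97.9% unadjusted at 129 and 160 per arm for 5.58 h, and 84.8%, 88.3% and 91.6% at 160 per arm for the 30% reduction with R² 0, 0.10 and 0.20.

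**4. Chance imbalance.** At 160 per arm a standardised baseline difference of up to 1.96 × √(2/160) = 0.219 SD is within ordinary chance. With R² = 0.10 this shifts the unadjusted estimate by 0.219 × √0.10 × 12.49 ≈ 0.87 h. The unadjusted interval, with half-width 1.96 × 1.396 = 2.74 h, already allows for it.

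**5. Index-visit admission.** A simulation used N = 320, intercept 0, an assumed conditional log odds ratio of −0.6, one standardised covariate and 800 replicates.

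| Covariate coefficient | Mean log OR, unadjusted → adjusted | SE | Power |
|---|---|---|---|
| 0.3 | −0.581 → −0.596 | 0.229 → 0.233 | 71% → 72% |
| 0.6 | −0.567 → −0.619 | 0.229 → 0.239 | 70% → 73% |
| 1.0 | −0.513 → −0.624 | 0.228 → 0.253 | 62% → 69% |

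The adjusted estimate moves away from zero because a conditional odds ratio is a different quantity from a marginal one. Power rises a little, but the standard error does not fall.

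**The case against.** **The planned test is not wrong.** A reader might infer that chance imbalance biases the primary result. The documents do not support that: under unstratified randomisation the two-sample comparison is unbiased with valid type I error, and its interval already covers chance imbalance. This stands in full.

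**The gain may be small.** A reader might infer a large power gain by starting from 103 per arm or by assuming that covariates explain up to 30% of the variance. The first misapplies follow-up attrition to an index-visit outcome, and nothing in the protocol supports the second. For the planned effect, the unadjusted test is already well powered. This also stands.

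**The pattern is coherent.** Index-visit outcomes (ED stay, index admission, satisfaction) are unadjusted; modelled follow-up outcomes, which are exposed to attrition, are adjusted. That could be a defensible reason, but the protocol does not state it, and it is no argument against adjusting the primary outcome. Nor is every follow-up outcome adjusted: mortality, duration of unplanned stays, costs and QALYs have no stated covariates.

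**Skew.** An SD close to the mean for a non-negative time makes the Wilcoxon route likely, and the power figures above do not describe that route. The remedy therefore replaces the model and does more than add covariates. Against this, the Outcomes section defines the endpoint as mean hours, and linear regression with a robust or bootstrap interval stays on that scale without needing normality.

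**Precision for admission.** A reader might expect a narrower interval there too. The simulation shows the opposite for the odds ratio.

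**Conclusion.** The point holds as one of efficiency and consistency. The primary outcome is analysed without covariates although the plan already uses age and baseline ISAR elsewhere, and no stratification is described.

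The benefit is modest for the planned effect: 0.4 to 3.2 percentage points of power at 129 per arm and 0.2 to 1.5 at 160. It is more useful for a smaller effect: with a 30% reduction at 160 per arm, about 3 to 4 points at R² 0.10 and about 7 at R² 0.20. All of this rests on the assumed R²; if age and ISAR barely predict ED stay, almost nothing is gained. For index-visit admission no gain in precision should be claimed.

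**What to change.** 1. Before any comparison by arm, prespecify as the primary analysis a linear regression of ED hours on arm, age and baseline ISAR score, reporting the adjusted mean difference with a robust or bootstrap 95% confidence interval.
2. Add Table 1 pathway and triage category if they are held as data. They are used for eligibility, but the protocol does not say that they are recorded as analysis variables.
3. Report the planned unadjusted test alongside as a sensitivity analysis.
4. For index-visit admission, report an age- and ISAR-adjusted odds ratio beside the unadjusted one, labelled as conditional.
5. Confirm that ISAR was scored before allocation was revealed. Data analysis calls it a baseline score, while Randomisation describes the baseline assessment as function and quality of life.

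**Cost.** No new patients are needed, and for age and ISAR no new data. The downside is that the primary model changes after recruitment closed on 31 May 2019 in a trial where patients and ED staff are not blinded. The change must therefore be dated and made without knowledge of results by arm. If that is no longer possible, keep the planned test as primary, give the adjusted model as supportive, and state why only follow-up measures were adjusted.

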The objectives of the study are as follows: 1) to implement an HSCP team including a whole time equivalent senior physiotherapist, senior occupational therapist and senior medical social worker in the ED at the University Hospital Limerick (UHL; Ireland) for a period of 6 months; 2) to examine if early assessment and intervention by the HSCP team improves the quality, safety, and clinical- and cost-effectiveness of care among older adults who present to the ED compared with usual care; and 3) to conduct a process evaluation for the HSCP intervention through focus group interviews with the HSCP team and representation from the wider ED staff regarding the implementation, delivery and acceptability of the intervention.

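### The stated primary test of ED stay ignores the Table 1 pathway, a baseline factor that fixes when the HSCP team may act; adjust for it and pre-specify an exploratory estimate in each pathway

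*Protocol article*

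**What the plan says.** **Two start points.** Table 1 (Participants) splits the eligible presenting complaints into two groups. For six of them (limb problems, falls, unwell adult, back pain, urinary problems, ear and facial problems) the team "will proactively treat these individuals without prior assessment by a physician". For the other four (chest pain, shortness of breath, abdominal pain, headache) the footnote reads: "The HSCP team will await medical clearance prior to assessment and intervention".

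**One clock.** Outcomes defines the primary outcome as "duration of patient ED stay (mean number of hours from time of arrival to discharge or admission". In the second group the wait for clearance therefore counts in the outcome but comes before the team may act.

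**One test.** Data analysis states: "Differences between the two groups in terms of ED length of stay and hospital length of stay will be analysed using an independent samples". The test meant is Student's *t* if normality holds, otherwise a Wilcoxon Mann–Whitney test with a bootstrapped interval for an effect size. No covariate is named. The same section does name covariates elsewhere: age and ISAR score for the follow-up logistic regressions, and these plus the baseline score in the ANCOVAs.

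**Randomisation.** "Computer-generated random numbers in blocks of 20 will be created using an internet-based system"; no stratification by pathway is stated.

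**Objective.** The second objective is "to examine if early assessment and intervention by the HSCP team improves the quality, safety" and effectiveness of care compared with usual care. Participants describes the trial as pragmatic.

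**The concern.** Pathway is a baseline factor of the protocol's own making. It is fixed by the presenting complaint, is recorded as part of eligibility, and determines how much of the measured stay the intervention can reach. It may also predict stay in its own right, because chest pain and a limb problem need not have the same work-up. A primary test that leaves it out gives up precision that costs almost nothing to obtain.

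The second issue is interpretation. If the effect differs between pathways, the pooled difference is an average weighted by the complaint mix recruited. A service planner reading that average could not tell whether a benefit came from input before the physician, input after clearance, or both. The Discussion says the findings will inform future implementation, so that reader is the intended one.

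**Working it through.** **Inputs from the protocol (Power calculation; Abstract).** Mean stay 13.95 h, SD 12.49 h; 40% reduction to 8.37 h, so the difference is 13.95 − 8.37 = 5.58 h; two-sided alpha 0.05; power 90%; 20% attrition; 258 patients (129 per group); recruitment target 320 (160 per group).

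**Inputs assumed.** The protocol gives no pathway shares, no mean stay by pathway and no effect by pathway. Ranges are shown for all three.

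**1. The plan's own figure.** A two-sample *t* test with 5.58/12.49 = 0.447 needs 107 per group for 90% power. 107 × 1.2 = 128.4, so 129 per group and 258 in total, as stated. It rests on one overall effect. With no loss, power at 129 per group is 95%.

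**2. Is the pooled test valid?** Simulation with no treatment effect, 258 patients, a 50:50 pathway mix, skewed (log-normal) stays and unstratified blocks of 20, 8,000 runs each:

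| Gap in mean stay between pathways | Type I error | Mean estimated difference |
|---|---|---|
| 0 h | 4.5% | 0.018 h |
| 4 h | 5.4% | 0.010 h |
| 8 h | 4.9% | −0.012 h |

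So there is no bias and no inflation. The chance imbalance in pathway share between arms had an SD of about 6 percentage points. With a gap of 4–8 h, an imbalance of that size moves a single trial's estimate by 0.06 × 4 = 0.24 h to 0.06 × 8 = 0.48 h. Adjustment removes this.

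**3. Precision left unused.** Let s be the share in the after-work-up pathway and g the gap in mean stay.

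Variance share = s(1 − s)g² / 12.49², with 12.49² = 156.0. Reduction in standard error = 1 − √(1 − variance share).

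| s | g | Variance share | Reduction in SE |
|---|---|---|---|
| 0.3 | 4 h | 0.21 × 16 / 156.0 = 2.2% | 1.1% |
| 0.5 | 4 h | 0.25 × 16 / 156.0 = 2.6% | 1.3% |
| 0.3 | 8 h | 0.21 × 64 / 156.0 = 8.6% | 4.4% |
| 0.5 | 8 h | 0.25 × 64 / 156.0 = 10.3% | 5.3% |

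At 129 per group the unadjusted SE is 12.49 × √(2/129) = 1.56 h, so the largest gain here takes it to about 1.47 h.

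**4. Dependence on case mix.** Pooled effect = 13.95 × [p × 0.40 + (1 − p) × r], where p is the before-work-up share and r the proportional effect after work-up.

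| r | p | Pooled effect | Power, 129 per group | Power, 160 per group |
|---|---|---|---|---|
| 40% | any | 5.58 h | 95% | 98% |
| 20% | 0.7 | 4.74 h | 86% | 92% |
| 20% | 0.5 | 4.19 h | 77% | 85% |
| 0% | 0.7 | 3.91 h | 71% | 80% |
| 0% | 0.5 | 2.79 h | 43% | 51% |

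If the effects are equal, case mix has no influence. The losses in the other rows follow from the assumed r.

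**5. What an analysis by pathway can deliver.** SE of the interaction = 12.49 × √[4/(Np) + 4/(N(1 − p))]. At p = 0.5:

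- N = 258: SE = 12.49 × √(16/258) = 3.11 h; for a 5.58 h difference in effect, power is 43%.
- N = 320: SE = 12.49 × √(16/320) = 2.79 h; power is 52%.

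The 95% interval within one pathway has a half-width of about 1.96 × 12.49 × √(2/64.5) = 4.3 h at N = 258, or 1.96 × 12.49 × √(2/80) = 3.9 h at N = 320.

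**6. The fallback.** A normal distribution with mean 13.95 and SD 12.49 would put about 13% of stays below zero (13.95/12.49 = 1.12 SDs). Skew is therefore likely, and so is use of the Mann–Whitney test. That test, as stated, has no place for pathway and does not estimate the difference in mean hours by which the outcome is defined.

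**The case against.** The strongest reply is that nothing here is in error. The aim is to compare a dedicated HSCP team with usual care in a pragmatic trial, and the Table 1 start rules are part of that service. Pathway is set before randomisation and occurs in both arms. This stands: the pooled comparison answers the stated question without bias.

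A reader might go further and infer that the trial cannot show whether early HSCP input works, or that conclusions about early care must be confined to the before-work-up pathway. The protocol does not support either. It never defines early as before a physician; the Background uses the word for HSCP teams in the ED generally, and the second objective applies it to the whole team. No objective sets early against late HSCP input. Input after clearance may still be earlier than usual care, where therapists attend only when called.

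A reader might also take the lower power figures above as a forecast. They are not. The protocol's 40% is an effect for the whole intervention group. Assigning it to one pathway and a smaller effect to the other assumes the dilution, and the 320 target softens it.

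The planning SD comes from all patients aged 65 and older at this ED, so variation between complaints is already in the sample size. This also stands: the gain from adjustment is extra precision, not repair of a shortfall.

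Finally, subgroup analyses and covariates are often left to an analysis plan that is not shown. For the estimates by pathway that is fair, and their absence is not an error. It does not cover the primary test, because the article states an unadjusted one while naming covariates for other outcomes.

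**Conclusion.** The point holds in a limited form. The primary test is valid for the HSCP service against usual care, but as stated it leaves out a recorded baseline factor that governs when the intervention can start. The price is modest: about 1–5% of the standard error, if mean stay differs by 4–8 h between pathways and 30–50% of patients are in the after-work-up pathway. If mean stay does not differ, the gain is essentially nil. Separately, the pooled result taken alone cannot attribute an effect, or its absence, to pre-physician input. That limits interpretation; it is not a flaw in the randomised comparison. How far the effect differs by pathway, if at all, cannot be judged from the protocol.

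**What to change.** 1. Keep the pooled arm difference in mean ED hours as the primary estimate. Fit it in a linear model with arm and Table 1 pathway (before v after medical work-up), with a bootstrap or robust 95% CI to allow for skew. Let this replace both the unadjusted *t* test and its Mann–Whitney fallback. If a rank test is kept, use a pathway-stratified one (van Elteren).
2. Pre-specify the arm difference with 95% CI in each pathway, labelled as an exploratory estimate and not a test.
3. Date and record the change before any comparison by arm is seen. Trial status says recruitment is complete, so stratified randomisation is no longer possible, but an analysis change is.

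No new data are needed, since the presenting complaint is part of eligibility. The cost is slightly more analysis work, one degree of freedom, and pathway-specific intervals too wide to settle whether the effects differ.
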